# AVATAR Virtual Reality Social therapy (AVATAR_VRSocial) for distressing voices and their interference in social everyday life in early psychosis: protocol of a single-blind parallel group randomised controlled feasibility study

**DOI:** 10.1136/bmjopen-2024-098004

**Published:** 2025-04-17

**Keywords:** Schizophrenia & psychotic disorders, Digital Technology, Psychosocial Intervention, Virtual Reality

## Abstract

**Introduction:**

Around 70% of people with psychosis experience auditory verbal hallucinations (AVHs), which can cause distress and impair the social functioning of the individual. AVATAR therapy works by facilitating a ‘face-to-face’ dialogue between the person and a digital representation (avatar) of their persecutory voice. Although there is cumulative evidence of this way of working with voices, enhancing the therapeutic focus on improved confidence and sense of control of the voices in social situations represents a promising way to boost generalisation of therapy gains into social contexts. We aim to enhance AVATAR therapy by incorporating immersive Virtual Reality (VR) social environments aiming to help the person to deal better with their voices in daily situations.

**Methods and analysis:**

A randomised controlled feasibility trial will be conducted. 40 patients aged 18 or above who are at early stages of psychosis (first episode of psychosis in the last five years) and report distressing and interfering voices will be recruited. Participants will be randomised to receive either a novel, enhanced version of AVATAR therapy (AVATAR_VRSocial) in addition to usual care or usual care alone. Assessor-blinded assessments will be conducted at baseline, 3 months (post-intervention) and 6 months (follow­-up). Key therapeutic targets of AVATAR_VRSocial will be those established by the previous evidence of this approach (ie, power and control, self-esteem and future focus), while introducing exposure and management of distressing voices during social interactions. Analyses will focus on feasibility outcomes (recruitment, retention and completion rates) and preliminary estimates of intervention effects. Qualitative interviews will be carried out with participants allocated to AVATAR_VRSocial to gain a comprehensive understanding of participants’ views on the acceptability of the intervention and research procedures. Thematic analysis of the qualitative interviews will assess the acceptability of the intervention, trial procedures and the new VR technology and software involved.

**Ethics and dissemination:**

The study has received ethical approval from the Ethics Commission at the Faculty of Psychology (Ruhr-Universität Bochum), and there is an independent Trial Steering Committee and Lived Experience Advisory Panel also supporting it. Findings will be disseminated through peer­-reviewed publications, conference presentations and science dissemination events.

**Trial registration number:**

ISRCTN35980117.

STRENGTHS AND LIMITATIONS OF THIS STUDYAVATAR_VRSocial represents the first attempt to enhance AVATAR therapy for distressing voices with the incorporation of innovative Virtual Reality technology to improve voice interference during daily life.The trial is the first to use this cognitive-relational approach and specifically focusing on distressing voices in people at early stages of psychosis (first episode of psychosis<5 years).The study uses mixed methods (clinical assessments, questionnaires, qualitative interviews) to respond to the research questions.Participants cannot be blinded to the treatment allocation, which could constitute a bias of the data.The control condition is *treatment as usual*, so it will not be possible to determine which elements of AVATAR_VRSocial may produce change.

## Background

 Auditory verbal hallucinations (AVHs) or *hearing voices* is the most prevalent form of hallucinations.^1 2^ Between 69% and 82% of individuals with schizophrenia spectrum disorders report experiencing them.^3^ The experience of negative AVH is not only a source of considerable emotional distress but has a significant impact on daily functioning and quality of life.^4^ Deterioration of social functioning manifests in avoidance and withdrawal from social interactions, both main characteristics of social anxiety. This is among the most prevalent and debilitating affective disturbances manifesting in people with psychosis, affecting around 25% of people with first episode of psychosis (FEP)^5^ and seriously hindering recovery.^6^ Particularly for those at early stages of psychosis, the stress associated with stigma^7^ and the distressing nature of the voices themselves—such as conveying a sense of danger—can lead individuals who hear voices to isolate themselves. Considering that such voices often belittle, intimidate and threaten voice-hearers, those affected face unique challenges in their everyday lives. These can range from difficulties disengaging from the voices, a fear of people’s perceptions should they react to the voices in public, struggling to concentrate on conversations with others or working out who is talking, to voices and their content triggering avoidance.^8 9^

While the current therapeutic gold standard for distressing voices, cognitive behavioural therapy for psychosis (CBTp), has shown small to moderate effects,^10 11^ studies suggest only around 50% of people with the disorder benefit from it,^12^ with very limited improvements in treatment response for AVH in recent years.^13^ CBTp is also lengthy and not widely accessible to many in need.^14^ AVATAR therapy is an innovative therapy approach designed to support voice hearers to develop an increased sense of power and control over their voices, through a series of dialogues between the person and a digital representation of the voice (or avatar). It was originally created by Julian Leff in 2013^15^ in the UK. Preliminary evidence for its efficacy was demonstrated through two independent pilot studies^16^,^15^ and further supported by the findings of a large fully powered randomised controlled trial (AVATAR1) comparing AVATAR therapy and supportive counselling.^17^ This study showed a post-therapy effect size of d=0.8 of AVATAR therapy on the primary outcome (total score on the Psychotic Symptom Rating Scales, auditory hallucinations subscale).^18^ Most recently, a multicentre randomised controlled study (AVATAR2) set out to test two versions of the therapy (a brief and extended form) against treatment as usual (TAU) with the aim to support optimisation. The study not only lends additional support to the efficacy of AVATAR therapy compared with TAU, but also shows that an abbreviated form of the therapy can yield similar clinical improvements in both voice distress and voice severity compared with a longer intervention.^19^ However, only AVATAR extended produced a significant reduction in voice frequency in this trial. Although effects on social functioning were not reported in the AVATAR1 RCT^17^ due to lack of suitable validated measures included within the assessment battery, participants who took part in the embedded qualitative study reported an increased level of engagement in social situations and improved confidence around others.^20^ Enhancing the therapeutic focus on improved confidence and sense of control of the voices in social situations represents a promising way to boost generalisation of AVATAR therapy gains into social contexts and reduce anxious avoidance and threat cognitions (including perceived threat from the voices).

Virtual Reality (VR) has long been used to facilitate exposure to feared stimuli mostly for anxiety disorders, with encouraging results for the treatment of psychosis.^21 22^ Virtual environments evoke responses in a participant that match those occurring in the natural environment. This offers a unique opportunity to access the user’s real-time behaviour, including interaction with virtual agents, and allows the person to test out new responses, for example, targeting the safety behaviours and paranoid attributions that can maintain voice-related distress.^23^ Relevant environments, providing emotionally significant content targeting specific emotions and related cognition for a specific population, and optimal induced levels of presence are required when delivering VR-based therapy. Following this evidence, we present a new augmented version AVATAR therapy which includes three additional sessions using VR environments to improve the generalisation of therapy gains to the person’s social functioning.

## Objectives

The primary objective is to assess the feasibility and acceptability of a targeted intervention to improve voices related distress, and social avoidance and distress in people at early stages of psychosis (FEP<5 years^24^). The second main research objective is to convene evidence on clinical outcomes to provide first estimates of efficacy of this enhanced version of AVATAR therapy (AVATAR_VRSocial) in a sample of German individuals with early psychosis, which can inform subsequent development and testing of the therapy. Table 1 summarises the objectives of the study and includes the associated feasibility markers and assessment measures.

**Table 1 T1:** Summary of objectives and related assessment measures

	Objectives	Measures
Primary	Assessing feasibility and acceptability of AVATAR_VR psychotherapy for people who experience distressing voice hearing	Number of patients referred to the study, consented, declined and retainedCompletion rates of each assessment measure and retention at follow-up assessmentsNumber and proportion of consenting participants within AVATAR_VRSocial condition who reach the point of therapy ‘exposure’ (attended at least five of nine therapy sessions)Number of adverse serious and non-serious adverse events in each condition
Secondary	Clinical information about preliminary estimates of clinical effectiveness of AVATAR_VRSocial in addition to treatment as usual vs treatment as usual alone in people in early stages of psychosis	Voice distress, frequency and severity of voices: PSYRATS-AHSocial anxiety and avoidance: O-AS, O-CDQOther voices measures: BAVQ-R; VPDS; Brief assessment of negative hallucinations when outsidePsychiatric symptoms: PSYRATS-DEL, DASS-21. CAINS, Rosenberg-Self-EsteemQuality of life: EQ-5D-5L
Qualitative	Assessing acceptability	AFIMFeedback from Qualitative Interview

AFIM, Acceptability and Feasibility of Intervention Measure; BAVQ-R, Beliefs About Voices Revised; CAINS, Clinical Assessment Interview for Negative Symptoms; DASS21, Depression Anxiety and Stress Scales; EQ-5D-5L, EuroQol BIOMED Research Programme; O-AS, Oxford—Agoraphobic Avoidance Scale; O-CDQ, Oxford Cognitions and Defences Questionnaire; PSYRATS-AH, Psychotic Symptoms Rating Scale—Auditory Hallucinations; PSYRATS-DEL, distress and frequency factors, and total scores on the delusional beliefs subscale of the Psychotic Symptoms Rating Scales; VPDS, Voice Power Differential Scale.

The hypotheses related to clinical outcomes are as follows:

Compared with TAU, AVATAR_VRSocial therapy added to usual care will reduce distress associated with voices (at post-treatment).Compared with TAU, AVATAR_VRSocial therapy added to usual care will reduce social avoidance and social distress (at post-treatment).Compared with TAU, AVATAR_VRSocial therapy added to usual care will reduce total voice severity, reduce psychiatric symptoms (depression, anxiety, negative symptoms), improve self-esteem and well-being, and enhance quality of life (at post-treatment).Treatment effects will be maintained at follow-up.

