Participants allocated to the AVATAR_VRSocial Therapy condition will further be asked to complete items regarding anxiety, perceived hostility, sense of presence and sensed presence at the end of each interaction with the avatar (adapted from refs.^39 40^). Following each VR session, participants will be asked to complete a short version of the State Social Paranoia Scale.^41^ Voice activity and content in the past week is monitored at the beginning of each session using select items of the PSYRATS-AH^18^ and the VPDS.^31^ After half of the sessions, participants will be asked to complete a measure of the therapeutic alliance (Working Alliance Inventory-Short Revised).^42^ Before starting the VR sessions, participants will be asked to complete the questionnaires related to social avoidance and social distress. After completion of the final session, participants will rate the acceptability and appropriateness of the therapy via the Acceptability of Intervention Measure and the Intervention Appropriateness Measure.^43^

A qualitative interview will be conducted with a subsample of consecutively recruited participants (n=10). This interview will take place once they have concluded their participation in all assessments in the trial. This interview will ask them for feedback on how they found the therapy, taking part in the trial and the technology/software involved. The interview will be conducted by a research worker or by a member of the Live Experience Advisory Panel with support from the research team.

Assessments and therapy sessions will be audio-recorded (after first establishing consent) to allow for assessment of adherence to the research protocol and assessment ratings. These will be stored securely on password-protected devices and then uploaded to the secure university server. Throughout the recruitment and research process, all efforts will be made to tailor to participants’ needs and preferences. Participants in the study will be reimbursed with a voucher worth €30 in online shopping portals for each baseline, post-therapy and follow-up assessments.

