### Trial interventions

#### AVATAR_VRSocial

AVATAR_VRSocial is an augmented version of the AVATAR therapy (as delivered in Craig *et al*^17^) by adding three additional sessions supported by immersive VR technology. Therefore, this therapy consists of a total of 10 sessions (see table 2).

**Table 2 T2:** Summary of the sessions including in AVATAR_VRSocial therapy

	Short description	Number of sessions
AVATAR therapy	Three-way dialogue between participant, avatar and therapist	Seven sessions (six sessions of + one assessment and avatar creation session)
Virtual Reality social scenarios	Interaction with social agents during quotidian situations+personalised negative voice	Three sessions

AVATAR therapy works by facilitating a novel therapeutic context in which a ‘face-to-face’ dialogue between the person and a computerised representation of their voice is facilitated by a therapist. Bespoke software transforms the therapist’s voice to match the pitch and tone of the chosen voice, and the person creates a visual representation of their voice. The voice and image are combined to produce the ‘avatar’ (ie, an animated talking virtual agent with enhanced lip-sync speech and eye blinking), through which the therapist interacts with the voice-hearer, in a three-way dialogue (for further details on the software, please see https://www.avatartherapy.co.uk/). Using this platform, the therapist can speak to the client in their normal voice or in the chosen avatar voice which is a modified version of their normal voice. Where there are multiple voices, the participant selects one to work with (usually the most dominant, frequent and distressing). The embodiment of the voice is enhanced using direct verbatim speech, and enactment of the ascribed character and background of the voice. A comprehensive account of therapeutic targets of AVATAR therapy showed that some therapeutic targets were clearly present for all therapy completers (power and control, self-esteem and future focus), whereas others (eg, maintenance processes, working with trauma, experiential disengagement) were identified in some but not all participants, in line with the tailoring of the intervention to an individualised formulation.^44^

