The virtual scenarios are presented using a wireless head-mounted display (Pico 4) with a resolution of 2160 × 2160 pixels per eye, 122.16° diagonal field of view and mounted headphones. The personalised negative voice is exported from the AVATAR therapy platform to the VR scenarios. The therapist can trigger the negative voice at random intervals (determined by the system) or at his/her own demand depending on the person’s performance. As per the AVATAR therapy sessions, the three VR sessions consisted of three parts: the pre-VR discussion with the therapist, the immersive part using the VR headset (lasting approximately 10 min) and the post-VR debrief with the therapist. The person can request to stop the immersive experience at any point.

At the end of the final session, participants will be asked to complete a self-reported questionnaire to assess the acceptability of the intervention.^43^ The number of active sessions attended (ie, sessions involving active avatar dialogue or VR practice) by the participant will be measured to assess treatment adherence. Fidelity to the clinical manual will be assessed by the therapist by completing a session-by-session checklist of specified targets (these will also be used during training and ongoing supervision; see above). Each session will be audio-recorded with consent. Therapist competence, after completion of training, will be assessed by an expert in AVATAR therapy for general/clinical and avatar-specific skills using ratings adapted from the first AVATAR therapy trial and allowing for differing skill requirements for each level of therapy.

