### Analysis

A sample size of n=20 per randomised group (n=40) will be sufficient to estimate a recruitment rate of 50% with a 95% CI of 34.51% to 65.9% and a retention rate of 80% with a 95% CI of 67.6% to 94.4% (PASS Software 2019). This sample size of 20 per arm will be sufficient to estimate the variability of the primary outcome measure (ie, changes in PSYRATS-AH and O-AS at post-treatment) for future sample size calculations, with 12 per arm sufficient for estimation of the variability for the purpose of sample size calculations.^47^ Difference between groups and 95% CI for the difference will be reported to aid sample size calculations for a definitive trial.

A complete statistical analysis will be drafted prior to recruitment beginning and finalised before any analysis is conducted. There will not be interim analyses or formal stopping rules in relation to this study as the primary goal is to establish feasibility parameters for a definitive trial. Data will be reported in accordance with the CONSORT principles, with the 2018 extension for reporting social and psychological intervention trials.^45^ We note recent CONSORT-SPI guidance, which recommends minimising the distinction between primary and secondary outcomes; therefore, all outcomes will be reported at the end of the trial.^48^ The feasibility data analysis and quantitative data analysis will be carried out by the MHRCT senior statistician clinical trials unit statistician and quality checked by a trial statistician.

Descriptive statistics will be used to summarise feasibility measures (ie, recruitment and retention, uptake of treatment, data completion) overall and by allocated group. Based on the ‘traffic light system/STOP-AMEND-GO’,^49^ progression criteria related to key feasibility outcomes such as recruitment, retention and treatment uptake rates have been proposed. Each criterion has ‘stop/amend/go’ indicators. For example, the progression criterion for treatment uptake will be 75% and above indicates the progression criterion has been met, 51–75% indicates the need to amend and below 50% indicates stop.

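### Therapy exposure (five of nine sessions) can be met without any VR session, so it does not show uptake of the component that is new

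*Protocol article*

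**What the plan says.** In the Objectives section, Table 1 lists the measures for the primary objective (feasibility and acceptability). One is the number and proportion of consenting participants in the AVATAR_VRSocial arm who reach exposure: "attended at least five of nine therapy sessions". It does not say which sessions must be among the five.

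The AVATAR_VRSocial section says the existing therapy is augmented "by adding three additional sessions supported by immersive VR technology" and that "this therapy consists of a total of 10 sessions". Table 2 describes the AVATAR part as "Seven sessions (six sessions of + one assessment and avatar creation session" and lists three VR sessions beside it. The same section measures adherence with one count: "The number of active sessions attended (ie, sessions involving active avatar dialogue or VR practice) by the participant will be measured to assess treatment adherence".

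The order of the two parts is given only indirectly. The Assessments section says: "Before starting the VR sessions, participants will be asked to complete the questionnaires related to social avoidance and social distress". The AVATAR_VRSocial section says that the VR scenarios are for practising what was learnt in the dialogues.

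The Analysis section offers one worked example of a progression rule: "the progression criterion for treatment uptake will be 75% and above indicates the progression criterion has been met". It places 51–75% in the amend band and below 50% in the stop band. The numerator of treatment uptake is not defined.

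**The concern.** The article presents the three VR sessions as what distinguishes this intervention from AVATAR therapy. The six-session dialogue therapy already has two pilot studies and a fully powered trial behind it (Background). A primary feasibility marker that the dialogues alone can satisfy does not show whether participants take up the added part.

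The population makes this more than a formality. Social avoidance is a treatment target, and the VR scenarios are a full bus, a full supermarket and a doctor's reception desk. Leaving before the VR sessions is a pattern that a feasibility study of this package should be able to detect in its headline attendance figure. The adherence count does not separate it out either, because it adds dialogue and VR sessions together.

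**Working it through.** **Inputs.** Dialogue sessions: 6. Assessment and avatar creation: 1. VR sessions: 3 (all Table 2). Exposure threshold: 5 of 9 (Table 1). Therapy arm: 20 of 40. Example go threshold for uptake: 75% (Analysis).

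**The plan's own figures.** Active sessions: 6 + 3 = 9, which reproduces the nine in Table 1. With the assessment session: 9 + 1 = 10, the total in the text. Nine and ten are therefore consistent if nine means active sessions, although the article does not say so in Table 1.

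**VR sessions forced by the threshold.** For a threshold of t active sessions, the fewest VR sessions compatible with meeting it is max(0, t − 6).
- t = 5: max(0, −1) = 0.
- t = 6: 0.
- t = 7: 1.

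On session count alone, a threshold of seven of nine would be the first to require a VR session. If the assessment session also counted, the expression is max(0, t − 7), and the first such threshold is eight.

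**If VR comes last.** With sessions attended in sequence, a participant who meets the threshold may stop after session 5, 6, 7, 8 or 9. Those who stop after 5 or 6 are exposed with no VR. Those who reach 7 or more have had at least one VR session.

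**Link to the uptake rule, if uptake means exposure (assumption).** Go needs 0.75 × 20 = 15 participants. At exactly 15 of 20 the article's go and amend bands both include 75%; 16 of 20 (80%) is clear of that overlap. So 15 to 20 participants could each attend five or six dialogues and no VR session, giving uptake of 75–100% with VR uptake of 0 of 20. The 95% Clopper-Pearson interval for 0 of 20 is 0 to 16.8%, and 0% lies in the article's stop band.

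**A milder case (assumed numbers).** If 16 of 20 reach five sessions and 6 of those stop before VR, five-of-nine uptake is 16/20 = 80%. VR-inclusive uptake is (16 − 6)/20 = 10/20 = 50%, which is below the amend band and on the edge of stop.

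**Chance of reaching 15 of 20.** Let p be the probability that a participant attends at least five dialogues, with participants independent. Then P(X ≥ 15), X ~ Binomial(20, p), is:

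| p (assumed) | P(X ≥ 15) |
|---|---|
| 0.70 | 0.42 |
| 0.80 | 0.80 |
| 0.90 | 0.99 |

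These probabilities come from dialogue attendance alone and hold even if nobody attends a VR session.

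**The case against.** Several points on the other side stand.

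- The Analysis section never says that treatment uptake is the five-of-nine measure. Exposure is the only attendance marker with a threshold in the article, so the link is a reasonable inference, but it remains one.
- A reader might infer that the whole trial could read go with no VR uptake. The article does not support this. Uptake is given as an example beside recruitment and retention, and the full set of criteria is not shown. Nor can one conclude that no VR-specific criterion exists in the full protocol.
- A reader might also infer that absence from VR would go unseen. It would not. A short paranoia scale follows each VR session, Table 1 counts completion of each assessment measure, a fidelity checklist is completed session by session, and acceptability ratings and interviews are planned. None of these, however, is shown as a go or stop criterion.
- Dialogue attendance is not uninformative. The article claims a second novelty, the focus on early psychosis, so whether these participants attend the dialogues is a fair feasibility question. A majority-of-sessions rule for the whole package is a defensible summary of that.
- The order of sessions is implied, not fixed, and no figure in the article says how many participants would stop before VR.

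These points limit the consequence. They do not change the fact that the stated threshold can be met without the added component.

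**Conclusion.** The definition of exposure does not require, and cannot by itself demonstrate, any contact with VR. That follows from the article's own session counts and needs no assumption. That people who stop after dialogue five or six would count as exposed rests on VR coming last, which two places in the article imply. That the uptake criterion could read go with VR uptake as low as 0 of 20 rests on uptake meaning five-of-nine exposure, and it concerns that one criterion, not progression of the trial as a whole. The 0-of-20 case is the logical limit; the actual gap depends on attendance that the article cannot tell us. This should be fixed, because the marker sits under the primary objective and the remedy is inexpensive, but it does not invalidate the trial.

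**What to change.** 1. State the numerator and denominator of the treatment uptake criterion, and say in Table 1 that nine means active sessions.
2. Keep five-of-nine exposure as a reported figure.
3. Add VR-inclusive exposure: at least five of nine active sessions, including at least one VR session. Apply the uptake stop/amend/go rule to it, or make it a separate criterion.
4. Report the number and proportion of the therapy arm attending at least one, at least two and all three VR sessions. One VR session is a minimal requirement and to some degree arbitrary, so the full breakdown should accompany it.

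No new data collection appears necessary: the session checklists and the scale after each VR session should identify VR attendance.

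The cost is more than a change of wording. Recruitment began in December 2023, so a prespecified criterion would be altered after the trial started, and protocol amendments go to the ethics committee. The change should be dated, disclosed and made before any analysis; the article says that the analysis plan is finalised before analysis, and data collection is planned to run to September 2026. Reported uptake may be lower than under the present definition.
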